### Secondary outcomes

1. Degree of change in auditory function

Complete recoveryFinal PTA in affected ear within 10 dB (≤10 dB) of PTA of baseline pure tone audiogram.OR should a baseline pure tone audiogram not be available:Final PTA in affected ear within 10 dB of PTA of unaffected ear (≤10 dB).OR should both ears be affected with hearing loss:Final PTA in affected ear within 10 dB of a normative reference (ISO7029).^13^Marked recoveryPTA improvement ≥30 dB (and final PTA in affected ear ≥10 dB of PTA of baseline pure tone audiogram).OR should a baseline pure tone audiogram not be available:PTA improvement ≥30 dB (and final PTA in affected ear ≥10 dB of PTA of unaffected ear).OR should both ears be affected with hearing loss:PTA improvement ≥30 dB (and final PTA in affected ear ≥10 dB of a normative reference (ISO7029)).^13^Slight recoveryPTA improvement ≥10 dB and <30 dB (and final PTA in affected ear ≥10 dB of PTA of baseline pure tone audiogram).OR should a baseline pure tone audiogram not be available:PTA improvement ≥10 dB and <30 dB (and final PTA in affected ear ≥10 dB of PTA of unaffected ear).OR should both ears be affected with hearing loss:PTA improvement ≥10 dB and <30 dB (and final PTA in affected ear ≥10 dB of a normative reference (ISO7029)).^13^No improvementPTA improvement <10 dB (and final PTA in affected ear ≥10 dB of PTA of baseline pure tone audiogram).OR should a baseline pure tone audiogram not be available:PTA improvement <10 dB (and final PTA in affected ear ≥10 dB of PTA of unaffected ear).OR should both ears be affected with hearing loss:PTA improvement of <10 dB (and final PTA in affected ear ≥10 dB of a normative reference (ISO7029)).^13^

2. Change in QoL score from initial presentation to follow-up at any one time between 6 and 16 weeks following treatment. QoL will be measured with the Hearing Handicap Inventory for Adults (HHIA) (for patients under 65 years of age) or Hearing Handicap Inventory for Elderly (HHIE) (for patients over 65 years of age) and the Health Utility Index Mark 3 (HUI3). QoL data will be collected from a subset of 20 trusts.

Out-of-limit thresholds obtained on the pure tone audiogram will be classified as a 96 dB loss at that specific frequency.

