### Inclusion criteria

Adult patients (man or woman) aged over 16 years of age presenting to NHS ENT and hearing services with a history of sudden hearing loss (within a 72-hour window) that is sensorineural in nature.

There is a decrease in hearing of ≥30 dB affecting at least three consecutive frequencies (between the following specific frequencies: 250 Hz, 500 Hz, 1000 Hz, 2000 Hz, 4000 Hz and 8000 Hz), using a premorbid pure tone audiogram as a baseline reference. Or should a baseline pure tone audiogram not be available, the unaffected ear can be used a baseline reference. Or should both ears be affected by hearing loss, a normative reference (ISO7029)^13^ can be used as the baseline reference.

Willing and able to provide written informed consent.

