### Candidate predictors for prognostic model

Age; gender; social class; presence of vestibular symptoms; precipitating illness; pattern of hearing loss; severity of hearing loss; time between onset of symptoms and treatment; treatment(s) received.

Pattern of hearing loss will be defined as: low frequency loss (250 Hz, 500 Hz and 1000 Hz), mid-frequency loss (500 Hz, 1000 Hz and 2000 Hz), high-frequency loss (2000 Hz, 4000 Hz and 8000 Hz) and all frequencies. Severity of hearing loss (on presentation) will be defined as follows: pure tone average (PTA) across six frequencies (250 Hz, 500 Hz, 1000 Hz, 2000 Hz, 4000 Hz and 8000 Hz), classified as: mild (25–40 dB loss), moderate (41–70 dB loss), severe (71–95 dB loss) and profound (>95 dB loss).

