### Primary outcome

The change in auditory function in the affected ear from initial presentation to follow-up (at any one time between 6 and 16 weeks from onset of symptoms). Auditory function will be defined as the PTA of air conduction thresholds between the following specific frequencies: 250 Hz, 500 Hz, 1000 Hz, 2000 Hz, 4000 Hz and 8000 Hz. If multiple pure tone audiograms have been carried out between 6 and 16 weeks, the most recent pure tone audiogram will be used for the calculation of auditory function.

Change in auditory function classified as:

Full recoveryFinal PTA in affected ear within 10 dB (≤10 dB) of PTA of baseline pure tone audiogram.OR should a baseline pure tone audiogram not be available:Final PTA in affected ear within 10 dB of PTA of unaffected ear.OR should both ears be affected with hearing loss:Final PTA in affected ear within 10 dB of a normative reference (ISO7029).

Partial to no recoveryFinal PTA in affected ear ≥10 dB of PTA of baseline pure tone audiogram.OR should a baseline pure tone audiogram not be available:Final PTA in affected ear ≥10 dB of PTA of unaffected ear.OR should both ears be affected with hearing loss:Final PTA in affected ear ≥10 dB of PTA of a normative reference (ISO7029).^13^

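### A final difference of exactly 10 dB falls in two recovery classes, and the 10 dB rule has no sign; the six-frequency average also merits a sensitivity analysis

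*Protocol article*

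**What the plan says.** Under Primary outcome, the protocol article measures auditory function as "the PTA of air conduction thresholds between the following specific frequencies: 250 Hz, 500 Hz, 1000 Hz, 2000 Hz, 4000 Hz and 8000 Hz". Full recovery is a final PTA within 10 dB of the reference, and for the premorbid audiogram the symbol ≤ is written out. Partial to no recovery uses ≥ for all three references; for the second reference it reads "Final PTA in affected ear ≥10 dB of PTA of unaffected ear".

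Secondary outcomes repeats this. Complete recovery carries ≤10 dB explicitly for the premorbid audiogram and for the unaffected ear. Marked recovery, Slight recovery and No improvement each add the condition "final PTA in affected ear ≥10 dB of PTA of baseline pure tone audiogram", or its equivalent for the other two references. The ≥ sign appears three times in the primary definition and nine times in the secondary one.

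Under Inclusion criteria, eligibility is set on individual frequencies: "There is a decrease in hearing of ≥30 dB affecting at least three consecutive frequencies". No minimum six-frequency PTA is required. The order of references (premorbid audiogram, unaffected ear, ISO7029) is the same as for the outcome. Candidate predictors for prognostic model includes pattern of loss, whose categories begin "low frequency loss (250 Hz, 500 Hz and 1000 Hz), mid-frequency loss (500 Hz, 1000 Hz and 2000 Hz", and severity of loss, which uses the six-frequency PTA.

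**The concern.** Full recovery is the event on which the sample size is based and which the prognostic model is to predict. Its two classes should exclude each other and cover every case. As written, one attainable value satisfies both. In the secondary outcome that value can satisfy both Complete recovery and No improvement, the two ends of the scale.

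The distance rule also has no direction. When the unaffected ear is the reference and has an older loss, the affected ear could end more than 10 dB better than it. Such an ear is not within 10 dB, and read literally it goes to partial to no recovery.

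A lesser matter is that eligibility looks at three or more frequencies while the outcome averages six. The same recovery per frequency can then produce different labels depending on how many frequencies were lost, and pattern and severity are both candidate predictors.

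**Working it through.** **Inputs from the article.** Full or complete recovery: difference ≤10 dB. All other classes: ≥10 dB. Six frequencies averaged. Eligibility: ≥30 dB at three or more consecutive frequencies. No improvement: PTA gain <10 dB together with a final difference ≥10 dB.

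**Assumptions not in the article.** Thresholds in 5 dB steps; the distribution of final differences; the level of the frequencies outside the loss.

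**1. The overlap.** Take a patient 15 dB from reference at presentation and 10 dB at follow-up, a gain of 15 − 10 = 5 dB.
- Full / Complete recovery: 10 ≤ 10, met.
- Partial to no recovery: 10 ≥ 10, met.
- No improvement: 5 < 10 and 10 ≥ 10, met.

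**2. Can exactly 10 dB occur?** With 5 dB steps and a measured reference, the mean of six differences moves in steps of 5/6 dB. Since 10 ÷ (5/6) = 12 whole steps, 10.0 dB is attainable. An ISO7029 reference need not lie on this grid, nor need an ear with an out-of-limit threshold recoded to 96 dB.

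**3. How many patients?** Share ≈ normal density at 10 dB × 5/6.

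| Mean, SD of final difference (dB) | Share | Of 510 |
|---|---|---|
| 15, 15 | 0.021 | 11 |
| 20, 20 | 0.015 | 8 |
| 25, 25 | 0.011 | 6 |
| 30, 25 | 0.010 | 5 |

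If differences are instead spread evenly over a span of 20 to 80 dB, the share is 1/(span ÷ (5/6) + 1): 1/25 = 4% at 20 dB and 1/97 = 1% at 80 dB.

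**4. Effect of averaging.** Starting PTA difference = (sum of the six differences)/6. Gain needed = start − 10. Residual allowed per affected frequency = 60/k for k affected frequencies. With a 30 dB loss at k frequencies and the rest at reference:

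| k | Start (dB) | Gain to reach 10 dB | Residual per affected frequency (dB) |
|---|---|---|---|
| 3 | 90/6 = 15 | 5 | 20 |
| 4 | 120/6 = 20 | 10 | 15 |
| 5 | 150/6 = 25 | 15 | 12 |
| 6 | 180/6 = 30 | 20 | 10 |

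The k = 3 row depends on the other three frequencies. If each is 5 dB worse than reference, the start is (90 + 15)/6 = 17.5 and the gain needed is 7.5 dB. If each is 5 or 10 dB better, the start is 12.5 or 10 and the gain needed is 2.5 or 0 dB. Three frequencies at 40 or 50 dB, with the rest at reference, need 10 or 15 dB.

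**5. Same recovery, different label.** Let every affected frequency go from 50 to 15 dB below reference. A three-frequency loss ends at 3 × 15/6 = 7.5 dB (full recovery). A six-frequency loss ends at 6 × 15/6 = 15 dB (partial to no recovery).

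**The case against.** The overlap is a small slip. The article writes out ≤ for full recovery, so the other bound was probably meant as >. Audiometry results go into one database, so a single rule can be applied to everyone. This stands as to size. It does not settle the wording, because ≥ is written consistently for every reference and both outcomes, and the text alone does not say which bound governs.

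A reader might infer that a gain under 10 dB is called No improvement by one scale and full recovery by the other. The article does not support that. No improvement also requires a final difference of at least 10 dB, so the two labels meet only at exactly 10.0 dB.

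A reader might also infer that a 5 dB change makes eligible patients fully recovered in general. That figure belongs to the eligibility minimum with the other three frequencies at reference, and there a gain of exactly 5 dB lands on the contested value. A 30 dB loss at all six frequencies needs 20 dB. The article does not show how many patients lie near the minimum.

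Finally, a reader might conclude that the six-frequency PTA is the wrong primary measure. A fixed set of frequencies judged by end state is a legitimate choice, and baseline pattern and severity may properly predict an end state in a prognostic model. Replacing it with an average over each patient's affected frequencies would select the worst thresholds at presentation (regression to the mean), give each patient a different metric and ignore new loss elsewhere. This objection stands in full against a replacement, but does not rule out a sensitivity analysis.

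**Conclusion.** The recovery classes overlap at exactly 10 dB in both the primary and secondary outcomes, and the distance rule lacks a sign. Both follow from the text without outside figures. The size of the overlap does rest on assumptions: about 1% to 2% of patients (5 to 11 of 510) with 5 dB steps and the normal distributions shown, or 1% to 4% under an even spread. How many patients the missing sign affects cannot be estimated from the article.

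The averaging effect is real arithmetic but is not an error in the plan. It is strongest for losses close to the three-frequency minimum and shrinks as more frequencies are involved. It bears on how the pattern and severity coefficients are read, and does not invalidate the outcome. Overall severity is minor to moderate.

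**What to change.** Define d = final PTA of the affected ear minus reference PTA, with sign. Full recovery and Complete recovery: d ≤ 10 dB. Partial to no recovery: d > 10 dB. Marked recovery, Slight recovery and No improvement: d > 10 dB plus their existing improvement bands. State this once for all three references. The classes then exclude each other and cover every value, and an ear that ends better than its reference counts as recovered. The cost is a wording correction before analysis, with no new data.

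Keep the six-frequency PTA as primary. Add a prespecified sensitivity analysis that recomputes the outcome with the PTA over the frequencies meeting the 30 dB criterion at presentation, and report how far the pattern and severity coefficients move. On that measure the minimum eligible patient starts at 30 dB and needs a 20 dB gain. Box 1 already lists audiometry results at both visits, so the cost is a little more analysis work. The report should note the regression-to-the-mean limitation of this version. A strict bound alone does not remove the averaging effect, so the two changes are separate.

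### Coding every out-of-limit threshold as 96 dB, with no cap on measured thresholds, can rank a no-response ear above a measurable one and reverse or understate graded recovery

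*Protocol article*

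**What the plan says.** The coding rule closes the Secondary outcomes section of the protocol article: "Out-of-limit thresholds obtained on the pure tone audiogram will be classified as a 96 dB loss at that specific frequency". It is worded for audiograms in general, so it is read here as applying to every pure tone average (PTA) in the study.

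Three other statements bear on it:

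- Primary outcome: "Auditory function will be defined as the PTA of air conduction thresholds between the following specific frequencies", followed by six frequencies from 250 to 8000 Hz. No upper cap on a measured threshold is given there or elsewhere in the article.
- Candidate predictors for prognostic model: severity at presentation is the same six-frequency PTA in bands, the top two being "severe (71–95 dB loss) and profound (>95 dB loss". The profound band has no upper end.
- Secondary outcomes: below complete recovery, grading is by PTA improvement. At least 30 dB is Marked, 10 to under 30 dB is Slight, and under 10 dB is No improvement.

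The article does not give the maximum output of the audiometers.

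**The concern.** An out-of-limit threshold means that the ear did not respond at the loudest level the instrument could deliver. At that frequency it should rank at or below the worst threshold the instrument can measure. A code of 96 dB does this only if nothing above 96 dB is ever measured. Otherwise a measured 110 dB enters as 110, while a worse ear with no response enters as 96.

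The value 96 is the lowest whole decibel in the profound band, so it works as a label for a single frequency. It does not work once it is averaged with measured thresholds or subtracted from them. At stake are the graded recovery outcome, where deterioration could be scored as recovery and real gain as none, and the severity predictor, which is one of the prespecified candidates for the prognostic model.

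**Working it through.** **Inputs from the protocol article.** Code for no response (NR) = 96 dB; PTA = mean of six thresholds; improvement cut-offs 10 and 30 dB; severe 71–95 dB, profound above 95 dB. The 96 is a convention, so there is no derived figure to reproduce.

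**Assumptions.** Instrument limit 105 or 120 dB, as a range. Reference PTA 20 dB, so that no example below counts as complete recovery.

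**Formula.** Improvement = presentation PTA − follow-up PTA. If *k* frequencies go from a measured *m* dB to NR and the rest do not change, the plan scores an improvement of *k*(*m* − 96)/6. This is positive for every *m* above 96. It reaches the 10 dB cut when *k*(*m* − 96) ≥ 60, which is *m* ≥ 106 for *k* = 6 and *m* ≥ 111 for *k* = 4.

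**Scores in dB and resulting grade:**

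| Presentation → follow-up | NR = 96 (plan) | NR = 105 | NR = 120 |
|---|---|---|---|
| 110 at all six → NR | 110 − 96 = +14, Slight | not measurable | −10, No improvement |
| 105 at all six → NR | +9, No improvement | 0, No improvement | −15, No improvement |
| Four at 115 → NR, two stay at 90 | 106.7 − 94.0 = +12.7, Slight | not measurable | −3.3, No improvement |
| NR at all six → 110 | −14, No improvement | not measurable | +10, Slight |
| NR at all six → 90 | +6, No improvement | +15, Slight | +30, Marked |
| NR at all six → 75 | +21, Slight | +30, Marked | +45, Marked |

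Third row: (4×115 + 2×90)/6 = 640/6 = 106.7 and (4×96 + 2×90)/6 = 564/6 = 94.0.

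The sign reverses at any measured value above 96. The grade reverses only if thresholds of about 106 dB or more are measured over most frequencies; with a 105 dB limit the worst case is +9 dB, which stays in No improvement. Starting from NR throughout, Slight needs a final PTA of 86 or less and Marked 66 or less. With NR at 105 these become 95 and 75; with NR at 120, 110 and 90.

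**Severity predictor.** Five NR frequencies plus one at 90 dB give (5×96 + 90)/6 = 570/6 = 95.0, severe. An ear measured at 100 dB throughout has PTA 100, profound, although it hears better at five of six frequencies. With NR at 105 the first ear is (5×105 + 90)/6 = 102.5; with NR at 120 it is 115.0. Both are profound, and the order is restored.

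**Primary outcome.** It compares the final PTA with a reference and does not use the presentation PTA. An ear with NR throughout (PTA 96) counts as full recovery only if the reference PTA is at least 96 − 10 = 86. The inclusion criteria require a loss of at least 30 dB at three consecutive frequencies. If those three are NR, the reference there is at most 96 − 30 = 66, and a reference PTA of 86 then needs the other three to average 106, since (3×66 + 3×106)/6 = 86. This is a corner case.

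**The case against.** The strongest reply is that everything rests on a limit the article does not give. If no instrument measured above 96 dB, the reversal would vanish, and at any single frequency with a limit below 96 the code already lies above every measurable value. The table's larger effects need high limits at most or all of the six frequencies. This stands as a condition on size. It does not remove the point, because the article's open-ended profound band leaves room for higher values and no sentence caps them.

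A second reply is that a condensed article may leave a cap to the full protocol or analysis plan. That is possible. But the article does state a coding rule, and as stated the rule does not preserve order.

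A third is that any ceiling hides change above it. This is true of the understated gains; the reversal is particular to this rule.

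Stronger readings are tempting but unsupported:

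- **That the primary outcome is compromised.** A reader might infer that a no-response ear is often counted as fully recovered. The eligibility rule makes this a corner case.
- **That the profound class is almost unreachable for partly measurable ears.** If 100 dB is measurable, four NR plus two at 100 average (4×96 + 2×100)/6 = 97.3, and five NR plus one at 95 average 95.8. Both are profound.
- **That the severity coefficient is biased towards zero.** Severity is categorical. The direction depends on how many ears change class and how those ears recover, and neither is known.

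**Conclusion.** The point holds in a conditional form. As written, the rule places no response below any measured threshold above 96 dB. If such thresholds are recorded, it can move patients by a grade or more on the secondary recovery outcome, and it can misorder ears at one boundary of the severity predictor.

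The shift is *k*(*m* − 96)/6 dB for deterioration to no response: 14 dB for six frequencies at 110 dB, 12.7 dB for four at 115 dB. For gain from no response to 90 dB, the understatement is at least 9 dB with a 105 dB limit and 24 dB with a 120 dB limit.

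This rests on two assumptions: that limits exceed 96 dB at enough frequencies, and that no unstated cap applies. The severity part also assumes that the rule covers presentation audiograms. The binary primary outcome is almost unaffected. The number of patients involved and the direction of any bias in the model cannot be derived from the article.

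**What to change.** Replace the 96 dB sentence with one fixed value per frequency, common to all sites and at or above the highest threshold measurable at that frequency on any study instrument. Apply it identically to presentation, follow-up and reference audiograms, and apply the severity bands on that scale.

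A code tied to each device's own maximum is not equivalent: across 97 trusts it could give identical ears different PTAs. Nor does the article show that the level at which no response occurred is recorded; Box 1 lists only audiometry results.

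As a sensitivity analysis, cap measured and out-of-limit values at the same ceiling at both visits. With a ceiling of 96, the 110 dB to no-response case scores 0 instead of +14. This removes the reversal, but no response to 90 dB still scores only +6, so change above the cap stays hidden.

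The cost is a revised sentence, a short per-frequency table, and a check of instrument limits across sites. Thresholds already entered as 96 must be identifiable as out-of-limit. No extra visits or patients are needed. The assigned value remains a convention, and where a site's own limit is lower, it may overstate gain from no response; the capped analysis helps to show how much this matters.

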### Statistical analysis

We will develop a prognostic model to predict recovery for patients with idiopathic SSNHL and assess the impact of idiopathic SSNHL on patients’ QoL. A multivariable prognostic model will be developed using the candidate predictors specified above (n=15). Missing outcome data at the end of the study will be imputed using multiple imputation by a chained equations procedure.^15^ Internal validation will be performed to quantify optimism in the predictive performance (calibration and discrimination) of the developed model using bootstrapping techniques. Bootstrapping techniques provide information on the performance of the model in comparable datasets and generate a shrinkage factor to adjust the regression coefficients.^16 17^

The mean change in HHIA, HHIE and HUI3 scores across patients with idiopathic SSNHL will be calculated from initial presentation to follow-up (any one time between 6 and 16 weeks). We will use the non-parametric Wilcoxon and McNemar–Bowker tests with a significance level of 5%. Statistical analysis will be carried out using R V.3.6.2 (R Foundation for Statistical Computing, Vienna, Austria).

### Study procedures

A summary of study procedures is outlined in figure 1. Box 1 provides a summary of all data to be collected. Adult patients with SSNHL presenting to any of the 97 NHS trusts will be assessed for eligibility. In 20 of 97 NHS trusts, all data identified in box 1 will be collected. In the remaining 77 trusts, all data except for QoL data will be collected. In centres where no QoL data are collected, there will be no deviation from the usual standard of care for any patient, and routinely collected patient data will be anonymised; therefore, consent is not required. For centres where QoL data are collected, patients will be provided with a study information sheet and requested to give written consent to participate in the study.

